## Abstract

**Introduction:**

Maintaining fluid intake sufficient to reduce arginine vasopressin (AVP) secretion has been hypothesised to slow kidney cyst growth in autosomal dominant polycystic kidney disease (ADPKD). However, evidence to support this as a clinical practice recommendation is of poor quality. The aim of the present study is to determine the long-term efficacy and safety of prescribed water intake to prevent the progression of height-adjusted total kidney volume (ht-TKV) in patients with chronic kidney disease (stages 1–3) due to ADPKD.

**Methods and analysis:**

A multicentre, prospective, parallel-group, open-label, randomised controlled trial will be conducted. Patients with ADPKD (n=180; age ≤65 years, estimated glomerular filtration rate (eGFR) ≥30 mL/min/1.73 m^2^) will be randomised (1:1) to either the control (standard treatment+usual fluid intake) or intervention (standard treatment+prescribed fluid intake) group. Participants in the intervention arm will be prescribed an individualised daily fluid intake to reduce urine osmolality to ≤270 mOsmol/kg, and supported with structured clinic and telephonic dietetic review, self-monitoring of urine-specific gravity, short message service text reminders and internet-based tools. All participants will have 6-monthly follow-up visits, and ht-TKV will be measured by MRI at 0, 18 and 36 months. The primary end point is the annual rate of change in ht-TKV as determined by serial renal MRI in control vs intervention groups, from baseline to 3 years. The secondary end points are differences between the two groups in systemic AVP activity, renal disease (eGFR, blood pressure, renal pain), patient adherence, acceptability and safety.

**Ethics and dissemination:**

The trial was approved by the Human Research Ethics Committee, Western Sydney Local Health District. The results will inform clinicians, patients and policy-makers regarding the long-term safety, efficacy and feasibility of prescribed fluid intake as an approach to reduce kidney cyst growth in patients with ADPKD.

**Trial registration number:**

ANZCTR12614001216606.

Strengths and limitations of this studyA major strength of the study is that it has a randomised controlled trial design and will provide high-level evidence regarding the long-term efficacy of prescribed water intake on the progression of autosomal dominant polycystic kidney disease.Other strengths include the duration of follow-up (3 years) and the use of height-adjusted total kidney volume as the primary outcome measure.Lastly, the study intervention will be implemented using a multipronged approach using self-monitoring, dietetic intervention and mobile phone technology.The limitations of the study are that the trial intervention is unblinded and is reliant on the behavioural change to drinking habits of the participant.

## Introduction

Autosomal dominant polycystic kidney disease (ADPKD) is the most common genetic kidney disease in adults, affecting one in every 2500 individuals, and the cause of kidney failure in 5%–10% of the dialysis population worldwide.^1^ It is due to heterozygous germline mutations in *PKD1* (85%) or *PKD2* (15%), which encode the transmembrane protein polycystin-1 and calcium ion channel polycystin-2, respectively.^1^ These proteins maintain the differentiated structure of the nephron during health and disease.^1^ The clinical hallmark of ADPKD is the presence of numerous nephron-derived cysts in the kidney, which form in early childhood and grow by 5%–10% per year, such that by midlife the kidney is about five times larger than normal (1.0 vs 0.2 kg),^2^ causing chronic pain and hypertension. The expanding cysts also compress healthy kidney tissue, leading to progressive chronic kidney disease (CKD) and renal replacement therapy in ~50% of affected people by age of 60 years.^3^ Currently, there is no ‘cure’ for ADPKD, and the ideal therapy to stop kidney cyst growth and prevent end-stage kidney disease (ESKD) will be one with few side effects, as it will need to be taken lifelong.^4^

Arginine vasopressin (AVP) is a posterior pituitary hormone with a recognised physiological role in maintaining water homeostasis.^5^ It is released in response to hypovolaemia and hyperosmolality, and binds to V_2_ receptors on the principal cells of the collecting duct in the kidney, causing reabsorption of water from the tubular lumen.^5^ Renal cysts are derived from the principal cells of the collecting duct of the nephron.^6 7^ However, the epithelial cells lining the cysts respond abnormally to AVP by activating intracellular cyclic adenosine monophosphate signalling, which stimulates proliferation and luminal fluid secretion, causing cyst growth. In rats, the congenital deficiency of AVP completely abrogated renal cyst formation and growth,^8^ providing compelling evidence that AVP has a critical role in cystogenesis and that its inhibition at an early stage of disease could markedly reduce the risk of developing ESKD in ADPKD. In this regard, small-molecule vasopressin-receptor antagonists have been shown to be highly effective in reducing cyst growth in preclinical studies,^9^ and in humans, a randomised controlled trial showed that 3 years of treatment with tolvaptan (a highly specific vasopressin-receptor antagonist) in early stages of ADPKD reduced the rate of increase in total kidney volume (TKV) by 50%, attenuated the decline in estimated glomerular filtration rate (eGFR) by 30% and reduced chronic kidney pain.^10^

For several years, it has been suggested that the suppression of AVP by increasing fluid intake could also slow renal cyst growth in ADPKD.^7 11^ In support of the hypothesis, preclinical experiments in the *pck* rat model of PKD showed that increased water intake reduced kidney enlargement,^12 13^ and comparison with separate studies imply that the efficacy might be similar (but with physiological differences) to vasopressin receptor antagonists.^14^ However, whether this hypothesis is also true in humans with ADPKD remains unknown. The data available are limited to a single post hoc analytical study,^15^ two short-term interventional trials (<1 week in duration) without control groups,^16 17^ and a single, small, quasi-randomised observational cohort study of 12 months’ duration, which paradoxically suggested that increased fluid intake increases renal cyst growth.^18^ Consequently, evidence-based clinical care guidelines have not included recommendations to increase fluid intake in patients with ADPKD and the matter remains controversial in clinical practice.^19^ Consistent with this view, patients with ADPKD attending a consumer workshop also stated that the role of fluid intake was an ambiguous area that needed urgent prioritisation in clinical research.^20^ An illustrative comment made by a workshop participant was: *‘there needs to be consistency of what doctors say about drinking less or drinking more’*.^20^

Two recent clinical studies reported that prescribed fluid intake could be achieved over a period of 2–4 weeks in patients with ADPKD.^21 22^ In addition, two randomised controlled trials are presently underway to address the role of fluid intake in ADPKD and CKD over a longer duration.^23 24^ However, neither of these studies will specifically address the long-term efficacy of fluid intake on renal cyst growth in ADPKD. Hence, the aim of the current study is to determine the efficacy and safety of prescribed water intake to *prevent* the progression of TKV in CKD (stages 1–3) due to ADPKD (PREVENT-ADPKD) over a 3-year period. The trial commenced study activity in 2015 and as of July 2017 75% of the planned target recruitment has been attained. The current paper provides a summary of the clinical trial protocol.

## Methods and analysis

### Participants, design and registration

This is a prospective, parallel-group, open-label, multicentre randomised controlled trial, which will enrol 180 participants that meet the inclusion criteria (table 1). The planned recruitment period is up to 1.8 years, and began at Westmead Hospital in December 2015. For participants, the duration of the trial is 3.2 years, including the screening visit and the run-in, treatment and post-treatment periods (figure 1). The trial is registered (Australian New Zealand Clinical Trials Registry number 1261-4001-216-606) and will be conducted according to Good Clinical Practice and reported using Consolidated Standards of Reporting Trials guidelines.^25^

**Table 1 T1:** Inclusion and exclusion criteria

Inclusion criteria	
1.	Adult patients providing informed consent, aged 18–65 years of age
2.	Diagnosis of ADPKD, such as meeting the Pei-Ravine criteria^52^
3.	eGFR (CKD-EPI) ≥30 mL/min/1.73 m^2^ within 6 weeks of randomisation
Exclusion criteria	
1.	Safety risk, eg, serum Na^+^ <135 mmol/L; requirement for medications with high risk of precipitating hyponatraemia, such as chronic use of diuretics; medical conditions that require fluid restriction, such as heart failure, chronic liver disease, nephrotic syndrome or generalised oedema; abnormalities in the voiding mechanism; pregnant or breastfeeding women
2.	Contraindication to or interference with MRI assessments (eg, ferromagnetic prostheses, aneurysm clips, severe claustrophobia or other contraindications)
3.	Risk of non-compliance with trial procedures (eg, history of non-compliance with medical therapy; history of substance abuse within the previous 2 years and/or participants who do not complete the required screening tests (24 hours urine, blood tests and baseline MRI) within 12 weeks of the screening visit)
4.	Concomitant conditions or treatments likely to confound end point assessments (eg, poorly controlled diabetes, other known causes of CKD, renal cancer, single kidney or severe comorbid illnesses)
5.	Participation in other clinical trials to slow ADPKD or CKD
6.	TKV Mayo Clinic subclass 1A on screening (low risk of progression)^53^

ADPKD, autosomal dominant polycystic kidney disease; CKD, chronic kidney disease; CKD-EPI, Chronic Kidney Disease Epidemiology Collaboration equation; eGFR, estimated glomerular filtration rate; TKV, total kidney volume.

**Figure 1 F1:**
[figure not shown]
Schema of the PREVENT-ADPKD trial design. Adapted from Torres *et al*.^10^

### Recruitment

Multiple strategies will be used to facilitate recruitment.^26 27^ Participants will be identified from nephrologists practising at the study centres (see below), either through direct referral to the study team (email or verbal communication) or review of clinic letters and (if available) local databases. This approach will be supplemented with presentations at the study centres and adjacent hospitals (such as Royal North Shore, Concord and Royal Prince Alfred Hospitals in Sydney). In addition, participants will also be recruited passively through the internet, digital and print media advertising (listing on the websites of the PKD Foundation of Australia, the Australasian Kidney Trials Network, Clinical Trials Connect and the University of Sydney; letters to Australian nephrologists, news items in the e-bulletins of Australian and New Zealand Society of Nephrology; newspaper advertisements; flyers placed in Renal Clinic waiting rooms in Sydney Hospitals). All identified and interested participants will be discussed with the treating nephrologist for their suitability and prescreened by telephone to tentatively determine their eligibility and verified using previous imaging and eGFR reports, prior to arranging their study visit.

### Mobile study team

To enhance the efficiency of the trial and minimise its impact on the local resources of the study centres, a mobile study team^28^ (based at the Westmead Institute for Medical Research and Westmead Hospital) consisting of research dietitians and a nephrologist, will visit the study centres to conduct research activity. The mobile study team will see several participants on the designated day of the visit, and be supported by local clinical research staff by provision of space and undertaking minor procedures such as blood collection.

### Study visits

*Screening visit (up to month 1.5)*. If a patient meets all inclusion criteria and no exclusion criteria, he or she will be enrolled in the trial. At this visit, participants will have their medical and ADPKD history reviewed, usual fluid intake and kidney pain (using the Halt Progression of Polycystic Kidney Disease (HALT-PKD) study group questionnaire)^29^ assessed. A venous blood sample and spot urine sample will also be collected for DNA analysis and biomarker assessment (see below). Due to the cost and time required to perform genetic testing, the effect of *PKD* mutation type on trial outcomes will be assessed retrospectively. Participants will then be asked to have two 24 hours urine collections and blood tests (for testing baseline electrolytes, eGFR and osmolality) as an outpatient at a local pathology collection centre, and a renal MRI (to assess baseline TKV) will be performed at an external radiology facility. The period from screening to randomisation visits (up to 12 weeks) will serve as the run-in period to confirm the participant’s willingness to adhere to study procedures.*Randomisation and baseline visit (month 0)*. Follow-up medical and ADPKD histories will be taken and venous blood and urine samples will be collected at this visit. Participants randomised to the control group will continue with their usual (ad libitum) water intake and standard treatment. Participants in the intervention group will be advised to adjust their daily water intake for the next 36 months, in addition to continuation of their standard treatment, and be provided with specific instructions, described in the section under *study intervention (group B)*.*Treatment period*. The 3-year treatment period includes repeat outpatient blood and 24 hours urine collections (at 3-monthly intervals in year 1 and 6-monthly in years 2–3), progress MRI scans (at 18 and 36 months) and visits to the study centre every 6 months.*Follow-up study visits (months 6, 12, 18, 24, 30 and 36)*. Progress medical and ADPKD histories and further collections of venous blood and urine will be undertaken at follow-up study visits. Study staff will record answers to specific questions on adverse events (AEs) and kidney pain (using the HALT-PKD questionnaire). In both groups, quality of life will be assessed 6-monthly (month 0, 6, 12, 18, 24, 30 and 36) and usual fluid intake will be assessed annually (month 0, 12, 24 and 36). At the final treatment visit at month 36, intervention group participants will be advised that they may return to their previous ad libitum water intake.*Post-treatment study visit*. This will occur at month 37 for all participants.

### Randomisation procedure

Participants will be randomly allocated in a 1:1 ratio (in permutated blocks of 4) to the control group or the intervention group, stratified by baseline eGFR (<60 or ≥60 mL/min/1.73 m^2^). Randomisation and concealed allocation will be performed with a secure, web-based randomisation service (Randomize.net). The trial statisticians have generated a validated randomisation list.

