### Proposed timeline and current status of the trial

The study has been in the development phase from 2012 to 2015, and trial recruitment commenced on 9 December 2015 (see table 3). In 2016, the model of a mobile research team was implemented and the active study centres included Westmead, Nepean and Norwest Private Hospitals in Western Sydney and Gosford Renal Research on the NSW Central Coast. In 2017, additional study centres commenced, and as of July 2017, 75% of the intended recruitment has been completed and 100% recruitment is anticipated by the end of 2017.

**Table 3 T3:** Proposed timeline of the PREVENT-ADPKD trial

Year	Milestone (*italics denote milestone has been completed*)
2012–2015	*Study protocol developed (V.4); Australian and New Zealand Clinical Trial registration; lead-site ethics committee approval; trial endorsed by AKTN; data and biostatistical management plan developed; DSMB appointed; randomisation list and electronic case report forms finalised; recruitment at Westmead Hospital started; intervention group supporting tools developed*
2016	*Commenced recruitment at Norwest Private Hospital, Nepean Hospital and Gosford Renal Research* *50% planned recruitment completed*
2017	*Commence recruitment at other Australian sites* *75% recruitment completed in July 2017* Plan to complete recruitment at the end of 2017
2018–2019	Follow-up of study participants
2020–2021	Last participant follow-up Study close-out, data analysis; report key findings

AKTN, Australasian Kidney Trials Network; DSMB, Data and Safety Monitoring Board.

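### A single stated block size of 4 in an open-label trial lets up to a third of assignments be deduced by staff who know it and track allocations, which could weaken concealment

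*Protocol article*

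**What the plan says.** The Randomisation procedure section of the protocol article gives one block size and one stratification factor: "Participants will be randomly allocated in a 1:1 ratio (in permutated blocks of 4") and "stratified by baseline eGFR (<60 or ≥60 mL/min/1.73 m^2"). Centre is not a stratum, so two sequences run across all centres. On concealment it says: "Randomisation and concealed allocation will be performed with a secure, web-based randomisation service". Varying block sizes are not mentioned.

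The design is unblinded: "This is a prospective, parallel-group, open-label, multicentre randomised controlled trial". Under Mobile study team, a team "consisting of research dietitians and a nephrologist, will visit the study centres to conduct research activity", with local staff in a supporting role, and "The mobile study team will see several participants on the designated day of the visit". Under Study intervention, the study dietitian starts the fluid prescription at the randomisation visit, so the allocation is known at once.

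Table 1 has an exclusion that needs judgement: "Risk of non-compliance with trial procedures (eg, history of non-compliance with medical therapy". Table 2 lists the eligibility criteria at screening and again at week 0. Under Proposed timeline, "as of July 2017, 75% of the intended recruitment has been completed". Under Measures to reduce bias, outcome assessors are blinded.

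**The concern.** In an unblinded trial, whoever sees the allocations can reconstruct the current block. With blocks of 4, once two participants in a block have gone to one arm, the rest of that block must go to the other. A web service conceals the list but does not prevent this deduction.

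Leaving centre out of the stratification usually helps, because local staff see only part of each sequence. A team that travels between centres to conduct the research may see much more of it.

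There is also some room to act on a prediction. The interval from screening to randomisation may be up to 12 weeks, so the order of randomisation has some play. Eligibility is rechecked at week 0 and includes a judgement about compliance. The run-in shows the team who is likely to adhere. If likely adherers were steered, even unconsciously, into a foreseen group B slot, the arms could differ in prognosis at entry. Blinded MRI reading does not correct this. Adjustment for baseline log10 ht-TKV removes only the part that baseline volume carries.

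**Working it through.** The article gives no figure for predictability, so there is none to reproduce. The inputs are the 1:1 ratio and block size of 4 (Randomisation procedure), the total of 180 (Sample size calculation) and 75% recruited by July 2017 (Proposed timeline).

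**1. Fully informed observer.** The six equally likely blocks are AABB, ABAB, ABBA, BAAB, BABA and BBAA.
- Positions 1 and 2 are never determined.
- Position 3 is determined when the first two match: 2 of 6 blocks, or 1/3.
- Position 4 is always determined.
- Determined share = (0 + 0 + 1/3 + 1)/4 = 33.3%.
- Number = 180 × 1/3 = 60, slightly fewer if a stratum ends mid-block.

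**2. Best-guess accuracy for the same observer.** By position the probability of a correct guess is 1/2, then 2/3, then (1/3 × 1 + 2/3 × 1/2) = 2/3, then 1. The mean is (0.500 + 0.667 + 0.667 + 1)/4 = 70.8%, against 50% by chance.

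**3. Partial sight.** Suppose the block position is known and each earlier allocation is seen independently with probability q. The next assignment is certain only if both members of the filled arm have been seen (probability q²). Share = (q²/3 + q²)/4 = q²/3. The article gives no value for q.

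| q (assumed) | Share certain | Of 180 |
|---|---|---|
| 1.0 | 33.3% | 60 |
| 0.9 | 27.0% | 49 |
| 0.75 | 18.8% | 34 |
| 0.5 | 8.3% | 15 |

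**4. Reach of the article's own disclosure.** Remaining in July 2017: 180 × 0.25 = 45. Determined among them, at full information: 45/3 = 15.

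**5. Alternative block schemes.** These come from a simulation of 4,000 runs of 90 assignments. The observer sees every earlier allocation and knows which sizes are possible, but not their order. Sizes are drawn with equal probability.

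| Scheme | Certain | Best guess correct |
|---|---|---|
| Fixed 4 (exact) | 33.3% | 70.8% |
| Random 4, 6 | about 5.6% | about 69% |
| Random 2, 4, 6 | about 4.0% | about 70% |
| Random 4, 6, 8 | about 2.3% | about 68% |

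The 45 remaining participants are split over two strata, so their sequences are shorter than 90. Repeating the 4, 6, 8 run with 22 assignments (about 45/2) gives about 2.4% and 67%, which leaves the comparison unchanged.

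**The case against.** A reader might infer that one team sees every allocation, that the block size is known to it, and hence that a third of assignments are certain in advance and concealment is undermined. The article does not support that reading.

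- It describes several dietitians and a nephrologist visiting centres. It does not say that one person attends or tracks every randomisation, or who randomised at the centres added in 2017.
- The trial statisticians generated the list. Nothing says recruiting staff were told the block size. The only disclosure shown is the article, written at 75% recruitment, and its publication date is not given.

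Both objections stand. They make 60 of 180 an upper bound.

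The routes for steering are also narrower than they first look. The several participants seen in one day may include follow-up visits. About 135 recruited (180 × 0.75) over roughly 20 months is about 7 a month, over two strata and several centres, so two same-stratum candidates facing a determined slot on one day would be occasional. By week 0 a participant has completed two 24-hour urine collections, blood tests and an MRI, so late exclusion for expected non-compliance would be unusual. This lowers the likely amount of steering but does not exclude it.

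Finally, predictability is not bias. eGFR is a stratifier, baseline log10 ht-TKV is the covariate, and mutation type is assessed only retrospectively, so these limit part of any effect. They do not cover expected adherence, which the run-in reveals.

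**Conclusion.** The point holds as a risk. A single small block size, two strata and open allocation make up to 33.3% of assignments (at most about 60 of 180) deducible by staff who know the block size and have followed all earlier allocations in the stratum. Under assumed partial sight the range is 27% to 8% for q from 0.9 to 0.5. The article's disclosure alone could affect at most about 45 participants and about 15 determined assignments.

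This could weaken allocation concealment. It does not show that concealment failed, and no bias in ht-TKV is shown or quantified. The conclusion rests on two things the article leaves open: whether recruiting staff knew the block size, and how much of each sequence they saw. The change is a worthwhile, low-cost improvement; the design is not invalid without it.

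**What to change.** For allocations still to be made, the trial statisticians should load a replacement list with randomly varying block sizes in the web service. The sizes should be withheld from recruiting staff and from publications until recruitment closes. Sizes 4, 6 and 8 are preferable to 2, 4 and 6: they cut certain assignments to about 2% and best-guess accuracy from 71% to about 68%, whereas including size 2 leaves accuracy at about 70%. The gain lies mainly in removing certainty; guessing accuracy falls only slightly under any of these schemes.

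As a sensitivity check over all 180 participants, compute each participant's predicted probability of group B from the earlier allocations in the stratum, using blocks of 4 for those randomised under the present list. Then test whether baseline covariates (for example log10 ht-TKV, eGFR, age and baseline urine osmolality) depend on it. This needs no new data and remains useful if recruitment has closed. It belongs naturally in the analysis plan, and its absence from the article is not a fault.

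The cost is a new validated list, one line in the protocol and slightly more possible imbalance at the end of a stratum. The list change reaches only the participants not yet randomised, about 45 as of July 2017.
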